### Randomization

After signed informed consent and baseline measurements are obtained, random allocation software (developed by M. Saghaei, M.D., at the Department of Anesthesia, Isfahan University of Medical Sciences, Isfahan, Iran) is used to assign a serial number to the 60 research volunteers and to randomly allocate 15 of them into each group. The serial number codes will be inserted into sealed, opaque envelopes, kept in a double-locked cabinet, and opened in the presence of the patient and a guardian.

### Implementation

A CRC will generate the allocation sequence, enroll participants, and assign participants to interventions.

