### Participant recruitment

For achieving adequate participant enrollment to reach target sample size, all stroke patients admitted to the Department of Neurology of Chonnam National University Hospital will be screened by Physical and Rehabilitation Medicine doctors. From among the first-ever patients with CI who are hospitalized and have finished treatment of early acute stage CI at the Department of Neurology, those who are assessed as stable by a neurologist and meet the inclusion and exclusion criteria will be recruited for participation in this study.

Patients who are given an explanation about this study by the Clinical Research Coordinator (CRC) and who voluntarily sign a consent form will be transferred to the Department of Physical and Rehabilitation Medicine to participate in this study (see Additional file 2). The CRC will continuously monitor the medical conditions of enrolled participants to improve adherence to intervention protocols.

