### Confidentiality and data management

Participant identification records will be kept confidential until the results of this study are published. All documents related to a clinical trial, such as case report forms (CRFs), will be recorded and labeled with participant identification codes and will not show the name of the participant. The serial number codes will be inserted in sealed, opaque envelopes, kept in a double-locked cabinet, and opened in the presence of the patient and a guardian.

All data of the participants will be recorded in Excel files by the CRC. Additionally, raw data (CRFs) will be kept in a cabinet until the end of this study.

Written informed consent will be obtained from the participants for publication of their individual details and accompanying images in this manuscript. The consent forms will be available for review by the Editor-in-Chief.

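### Allocation concealment is not secured against the research coordinator, who generates the sequence, enrols the patients and assigns them

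*Protocol article*

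**What the plan says.** Four sections of the protocol article bear on this.

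- **Implementation** consists of one sentence: "A CRC will generate the allocation sequence, enroll participants, and assign participants to interventions".
- **Participant recruitment** puts the coordinator (CRC) in contact with the patient before consent: "Patients who are given an explanation about this study by the Clinical Research Coordinator (CRC) and who voluntarily sign a consent form" are then transferred to the rehabilitation department to take part. The same section gives screening to others ("all stroke patients admitted to the Department of Neurology of Chonnam National University Hospital will be screened by Physical and Rehabilitation Medicine doctors") and brings in a neurologist's judgement ("those who are assessed as stable by a neurologist and meet the inclusion and exclusion criteria will be recruited").
- **Randomization** places allocation at a set point, "After signed informed consent and baseline measurements are obtained", and describes the concealment device: "The serial number codes will be inserted into sealed, opaque envelopes, kept in a double-locked cabinet, and opened in the presence of the patient". The guardian is to witness this too. Totals are fixed at 15 in each of four groups. No holder of the list or of the cabinet keys is named.
- **Blinding** says that the CRC, the treating practitioner and the assessor are separate people. Against selection, performance and attrition bias it relies on staff being free of conflicts of interest and preconceptions.

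**The concern.** Concealment requires that whoever brings patients into the trial cannot know which arm comes next. Implementation gives the making of the list and the enrolment of patients to one role. This is a stated rule, so it cannot be put down to the brevity of a journal article.

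What is at stake is who enters each arm. Someone who knows the next arm can, without any intent to mislead, explain the study more or less persuasively or bring one candidate forward before another. Assessor blinding acts only after entry and does not protect against this. Patients and practitioners are unblinded, so the randomisation itself carries much of the trial's protection against bias. An imbalance in measured baseline scores can be seen and to some extent allowed for. An imbalance in prognosis that nobody measured can be neither seen nor corrected.

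**Working it through.** The protocol gives no figure on this point to reproduce. The check compares the sections and adds a small calculation as illustration.

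**1. Who could know the sequence, and at which step they act**

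| Step | Who acts | Hidden by the envelopes? |
|---|---|---|
| Generate the list | CRC (Implementation) | No: this person makes it |
| Screen admissions | Rehabilitation doctors (Participant recruitment) | Yes |
| Judge stability | Neurologist (Participant recruitment) | Yes |
| Explain the study before consent | CRC (Participant recruitment) | No |
| Enrol and assign | CRC (Implementation) | No |
| Open the envelope | In front of patient and guardian (Randomization) | Yes, for patient and guardian |
| Treat; assess | Separate practitioner and assessor (Blinding) | Yes, until allocation |

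The envelopes work for every role except the one that explains the study and enrols. No section says that the CRC is kept from the list, and none says that somebody else holds it.

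**2. Whether Blinding closes the gap.** The separation there runs between CRC, practitioner and assessor. The separation needed is between the list maker and the enroller, and both of these are the CRC. A statement that staff have no conflicts of interest is an assurance about people and does not keep the list from anyone.

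**3. Room for choice in order of entry.** Sample size gives an average of 46 cerebral infarction patients a month, of whom 10–20% would be treated in the rehabilitation department and be eligible:

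46 × 0.10 = 4.6 and 46 × 0.20 = 9.2 candidates a month.

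Several candidates may therefore be available at about the same time, and their order of entry is not fixed by events.

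**4. How predictable the next arm is**

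- Complete concealment with no knowledge of past assignments: 1/4 = 25%, or 15 of 60.
- Past assignments known but no list, always guessing the arm with most places left: 34.8% on average over 4,000 simulated lists, or about 0.348 × 60 = 21 of 60. This assumes one random ordering of 60 with 15 per arm, since no block size is stated.
- List known: 100%, or 60 of 60. This assumes that the list is made before patients are enrolled.

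The gap attributable to the combined role is therefore between about 35% and 100%. The step from 25% to 35% comes from the fixed totals and would remain for anyone who follows past assignments.

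**The case against.** The case on the other side has real content.

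- **The envelopes do something.** A reader might infer that allocation is not concealed at all and that the envelopes are worthless. The text does not support that. They can hide the sequence from screening doctors, neurologist, practitioners, assessor and patients. Opening them in front of patient and guardian, after consent and baseline, also makes an unseen swap harder.
- **The CRC is not described as choosing candidates.** A reader might infer that the CRC decides whom to approach. Participant recruitment says that all stroke admissions to neurology are screened by rehabilitation doctors and that a neurologist judges stability. The CRC's documented part is explanation, enrolment and assignment. That leaves consent and order of entry open to influence, which is narrower.
- **Timing is ambiguous.** Read literally, Randomization has the software used after consent and baseline, in which case there may be no list to consult beforehand. Prepared envelopes in a locked cabinet, and a single allocation of 60 people into groups of 15, point to a list made in advance. The text does not settle it, so the 100% is conditional.
- **The bias cannot be sized.** With 15 per arm, the standard error of a difference between two arm means is √(2/15) = 0.365 SD, and one could set an assumed shift in baseline Fugl-Meyer score against it. The document supports no such shift. The primary outcome is also change in that score, with baseline among the repeated measures, so a baseline shift would not carry over one for one.
- **The trial is a pilot.** This limits what will be concluded from it but does not explain why one role should do both tasks. Nor does the possibility that "A CRC will generate the allocation sequence, enroll participants, and assign participants to interventions" covers more than one coordinator: no division within the role is stated, and other sections write of the CRC as one.

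The CRC's data entry and adverse event recording are separate matters and form no part of this point.

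**Conclusion.** The concern stands in limited form: concealment is not secured against the CRC. The envelopes protect against other people, and the role separation under Blinding does not reach the gap.

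In size, the CRC's foreknowledge could be complete (100%), where someone without the list would reach about 35%. This rests on two assumptions: that the list precedes enrolment, and that the CRC is one person or one undivided role. Both are the more natural reading, but neither is stated outright. Nothing in the document shows that steering has occurred, and no amount of bias in the Fugl-Meyer comparison can be derived from it. What can be said is that selective consent or ordering could pass unnoticed with 15 per arm, and that no later analysis could correct its effect on unmeasured prognosis. That justifies changing the procedure while enrolment continues; Trial status describes the trial as ongoing.

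**What to change.** Amend Implementation so that an existing team member with no role in recruitment, treatment, assessment or data entry generates the sequence, holds it, and prepares sequentially numbered opaque envelopes. State that the CRC has no access to the list and opens the next envelope only once consent and baseline measurements are complete. The timing of that last step is already in Randomization and needs only to be kept.

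If patients have already been entered, regenerate the remaining allocations in the same way, within the places left in each arm. Then reconcile Randomization, Implementation and Blinding, so that they agree on when the list is made, who holds it, and that the list maker and the enroller are different people.

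The cost is a short amendment and the reassignment of a one-off task. The change does not remove the modest predictability that comes from fixed totals of 15 per arm.

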### Blinding

We have no choice but to adopt a single blinding (outcome assessor blinding) approach, as sham treatment — where participants and practitioners are not aware of the treatment condition — is impossible due to the characteristics of scalp acupuncture which include scalp penetration. Efforts to maintain objectivity are made by separating the CRC who manages the treatment schedules, the practitioner who conducts the treatments, and the assessor. During the course of this clinical trial, the assessor will not come into contact with any of the participants except at the time of assessment. Further, there is no circumstance where unblinding will be permitted. To prevent risks of bias, such as selection, performance, and attrition caused by non-blinding of participants and practitioners, only individuals without conflicts of interest or preconceived positions are involved in this study. All practitioners will receive training in clinical trials prior to participation in this study.

### Intervention

All participants will receive occupational therapy, which focuses on practicing fine and gross motor movements, activities of daily living, task-oriented therapeutic exercises, and muscular electrical stimulation therapy, as needed. Training for swallowing and to improve language will be also performed for dysarthria. These sessions will be conducted for 30 min, twice daily (excluding Saturdays and Sundays) for 3 weeks, for a total of 15 times. SA, rTMS, and SAEM-CS therapies will be conducted once daily for 20 min (excluding Saturdays and Sundays) for 3 weeks, for a total of 15 times (see Table 2).

**Table 2 Tab2:** Three-week treatment protocol (example for a patient admitted on a Monday)

		Monday–Friday	Saturday, Sunday	Monday–Friday	Saturday, Sunday	Monday–Friday		Four weeks after intervention completion
Morning	Admission Assessment at baseline	Physical therapy (30 min)	No treatment	Physical therapy (30 min)	No treatment	Physical therapy (30 min)	Discharge Assessment at the end of intervention	Follow-up assessment
		Occupational therapy (30 min)		Occupational therapy (30 min)		Occupational therapy (30 min)		
		Functional electrical stimulation (30 min)		Functional electrical stimulation (30 min)		Functional electrical stimulation (30 min)		
Afternoon		Physical therapy (30 min)		Physical therapy (30 min)		Physical therapy (30 min)		
		Occupational therapy (30 min)		Occupational therapy (30 min)		Occupational therapy (30 min)		
		Functional electrical stimulation (30 min)		Functional electrical stimulation (30 min)		Functional electrical stimulation (30 min)		
		SA group: SA therapy rTMS group: rTMS therapy SAEM-CS group: SAEM-CS therapy		SA group: SA therapy rTMS group: rTMS therapy SAEM-CS group: SAEM-CS therapy		SA group: SA therapy rTMS group: rTMS therapy SAEM-CS group: SAEM-CS therapy		

The SA therapy method will be conducted as follows: one or two needles are horizontally inserted about 3 cm deep at the lesion site and upper limb regions of MS6 (line connecting GV21 and GB6) and MS7 (line connecting GV20 and GB7) [8] under the Standard International Nomenclature in the direction from GV21 to GB6 and GV20 to GB7. Manual stimulation and electroacupuncture are not applied, and the needles (KOS-92 non-magnetic steel acupuncture needles; size 0.25 mm × 30 mm; Dong Bang Acupuncture, Inc., Boryeong, Republic of Korea; Product no: A84010.02) (see Table 3) are left in position for 20 min (see Table 4).

**Table 3 Tab3:** KOS-92 alloy distribution

Type	C	Si	Mn	P	S	Ni	Cr	N	Mo	Other	Note
STS304	0.08	1.0	2.0	0.045	0.03	8–10.5	18–20				
STS304N1	0.08	1.0	2.5	0.045	0.03	8–10.5	18–20	0.1–0.25			
STS316	0.08	1.0	2.0	0.045	0.03	10–14	16–18		2–3		
KOS-92	0.08	1.0	10	0.03	0.03	5–6	17–18	0.25–0.35			Non-magnetic

Unit: %

**Table 4 Tab4:** Revised Standards for Reporting Interventions in Clinical Trials of Acupuncture (STRICTA)

	Item criteria	Description
1. Acupuncture rationale	1a) Style of acupuncture	Korean medicine therapy
	1b) Reasoning for treatment provided, based on historical context, literature sources, and/or consensus methods, with references where appropriate	1) Discussion among four doctors who practice Korean medicine (consensus) 2) Textbook of acupuncture and moxibustion medicine 3) Relevant articles [7, 8] Selection of treatment regions based on textbooks, related papers, and expert discussions
	1c) Extent to which treatment varied	Standardized treatment
2. Details of needling	2a) Number of needle insertions per subject per session (mean and range where relevant)	2–4
	2b) Names (or location if no standard name) of points used (uni-/bilateral)	SIAN’s MS6; MS7 of the lesional hemisphere
	2c) Depth of insertion, based on a specified unit of measurement or on a particular tissue level	Needles were horizontally inserted into the subcutaneous tissue of the scalp, about 3 cm deep.
	2d) Responses sought	No de qi or muscle twitching — only sensation due to needle insertion
	2e) Needle stimulation	None
	2f) Needle retention time	20 min per session
	2 g) Needle type	KOS-92 non-magnetic steel disposable needles (0.25-mm diameter and 30-mm length), manufactured by Dong Bang Acupuncture, Inc.
3. Treatment regimen	3a) Number of treatment sessions	15
	3b) Frequency and duration of treatment sessions	Five times/week for 3 weeks, 20 min per session
4. Other treatment components	4a) Details of other interventions administered to the acupuncture group	Conventional stroke rehabilitation therapy
	4b) Setting and context of treatment, including instructions to practitioners, as well as information and explanations given to patients	Practitioner-patient conversation about the context of the treatment, life habits, and daily life management
5. Practitioner background	5) Description of participating acupuncturists	Korean medicine doctor with the following qualifications: 6 years of formal university training in Korean medicine, a license, and at least 2 years of clinical experience
6. Control or comparator interventions	6a) Rationale for the control or comparator in the context of the research question, with sources that justify the choice	Wang Y, Shen J, Wang XM, Fu DL, Chen CY, Lu LY, et al. Scalp acupuncture for acute ischemic stroke: a meta-analysis of randomized controlled trials. *Evid Based Complement Altern Med* 2012;2012:480950; Lee SJ, Shin BC, Lee MS, Han CH, Kim JI. Scalp acupuncture for stroke recovery: a systematic review and meta-analysis of randomized controlled trials. *European J Integr Med*. 2013;5:87–99
	6b) Precise description of the control or comparator; details for items 1–3 above with the use of sham acupuncture or any other type of acupuncture-like control	Conventional stroke rehabilitation therapy for control, rTMS, and SAEM-CS groups. LF-rTMS applied to the hot spot of the M1 region (the motor cortex at the contralesional hemisphere) for the rTMS group and LF-rTMS applied to the same M1 and simultaneous SA stimulation over the upper MS6 and MS7 regions of the lesional hemisphere for the SAEM-CS group

The rTMS method will be conducted as follows: a 70-mm figure 8 coil and a Magstim Rapid stimulator (Magstim Co., Dyfed, UK) is used to deliver 1 Hz of rTMS to the skull of the contralesional hemisphere at the site that elicits the largest motor evoked potentials (MEPs) in the first dorsal interosseous (FDI) muscle of the unaffected upper limb. One LF-rTMS session consists of 1200 pulses and lasts for 20 min. The stimulation intensity is set to 80 % of the motor threshold of the FDI muscle, which is defined as the lowest intensity of stimulation that provokes MEPs [15, 16]. All patients sit in a reclining wheelchair and are asked to relax as much as possible, with their heads strapped to a headrest [9].

The SAEM-CS treatment method will be conducted as follows: the above-described SA and LF-rTMS therapies are performed simultaneously. After SA treatment of MS6 and MS7 on the lesion side, LF-rTMS stimulation is conducted on the contralateral hemisphere of the opposite side of the lesion for 20 min (Fig. 2).

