**Methods/design:**

This study is a prospective, outcome assessor-blinded, randomized controlled clinical trial with a 1:1:1:1 allocation ratio. Participants with motion or sensory disabilities caused by a first-time cerebral infarction (*n* = 60) that had occurred within 1 month of the study onset will be randomly assigned to control, SA, rTMS, or SAEM-CS groups. All groups will receive two sessions of conventional rehabilitation treatment per day. The SA group will receive SA on the upper limb area of MS6 and MS7 (at the lesional hemisphere) for 20 min, the rTMS group will receive low-frequency rTMS (LF-rTMS) treatment on the hot spot of the M1 region (motor cortex at the contralesional hemisphere) for 20 min, and the SAEM-CS group will receive LF-rTMS over the contralesional M1 region hot spot while receiving simultaneous SA stimulation on the lesional upper limb area of MS6 and MS7 for 20 min. SA, rTMS, and SAEM-CS treatments will be conducted once/day, 5 days/week (excluding Saturdays and Sundays) for 3 weeks, for a total of 15 sessions. The primary outcome will be evaluated using the Fugl‐Meyer Assessment, while other scales assessing cognitive function, activities of daily living, walking, quality of life, and stroke severity are considered secondary outcome measures. Outcome measurements will be conducted at baseline (before intervention), 3 weeks after the first intervention (end of intervention), and 4 weeks after intervention completion.

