### Study design

This study is a prospective, outcome assessor-blinded, single-center, randomized controlled clinical trial with a 1:1:1:1 allocation ratio. This study is a pilot study to investigate the efficacy and safety of SAEM-CS, which is a newly developed treatment. This study is designed as a single-center study to overcome several procedural and organizational difficulties in terms of developing a research team, since SAEM-CS involves the simultaneous conduction of SA and rTMS. Participants (*n* = 60) who fit the inclusion and exclusion criteria will be randomly allocated into a control group (*n* = 15), SA group (*n* = 15), rTMS group (*n* = 15), and SAEM-CS group (*n* = 15). All groups will receive conventional stroke rehabilitation therapy twice/day, five times/week (excluding Saturdays and Sundays), for a total of 15 times over the course of a 3-week hospitalization period at Chonnam National University Hospital. In addition, the SA group will receive SA therapy, the rTMS group will receive rTMS therapy, and the SAEM-CS group will receive SAEM-CS therapy once/day. Outcome measures will be determined at baseline (before intervention), 3 weeks after the first intervention (end of the intervention), and 4 weeks after completion of the intervention.

This study was approved by the Ministry of Food and Drug Safety (MFDS), Medical Device Clinical Trial Plan Approval number 516. (See Additional file 1.)

The study design is summarized in Table 1 and Fig. 1.

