### Data analysis

Continuous data will be presented as means and standard deviations, while categorical data will be presented as frequencies and percentages. A repeated measures ANOVA will be conducted for the FMA and all secondary outcomes (NIHSS, MBI, FIM, K-MMSE, 9HPT, ASHA-NOMS, FAC, EQ-5D, MAS, Hand Grip Strength, and MEPs). Dependent variables include measured values before and after intervention and the measured values 4 weeks after completion of intervention. An *F* test will be conducted to detect differences between therapies, and Tukey’s post hoc test will be conducted to identify the groups. Repeated contrast tests will be conducted to account for time differences in each group, and the interaction group and time test will be conducted. A *p* value of <0.05 will be considered significant, and participants who drop out of the study will be excluded from the analysis. In brief, only complete case analyses will be used; thus, only subjects who complete the three evaluations will be analyzed. All statistical analyses will be performed using SPSS version 22.0 software (SPSS Inc., Chicago, IL, USA).

Data from participants who engage in less than 70 % of protocol adherence (i.e., receive <10 treatments from 15 trials) will be eliminated. Missing values will be implemented by multiple imputations. In addition, statistical differences will be verified by comparing attribution between eliminated and completed participants to check particular factors causing drop-out.

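### The adherence exclusion rule gives two thresholds as one: below 70 % of 15 treatments means 10 or fewer, but the stated count removes only 9 or fewer

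*Protocol article*

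**What the plan says.** The rule is in the Data analysis section of the protocol article: "Data from participants who engage in less than 70 % of protocol adherence (i.e., receive <10 treatments from 15 trials) will be eliminated". The words in parentheses are offered as the meaning of the percentage, not as a second rule.

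The 15 matches the schedule of the added therapies, which the Intervention section gives once a day on weekdays over three weeks, 15 sessions in all. The control arm has none of these therapies and receives conventional rehabilitation only. For that, Study design says "All groups will receive conventional stroke rehabilitation therapy twice/day, five times/week (excluding Saturdays and Sundays), for a total of 15 times" and Intervention says "These sessions will be conducted for 30 min, twice daily (excluding Saturdays and Sundays) for 3 weeks, for a total of 15 times". The Abstract puts it as "All groups will receive two sessions of conventional rehabilitation treatment per day".

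On content, the Intervention text names occupational therapy and offers "muscular electrical stimulation therapy, as needed". Table 2 lists physical therapy, occupational therapy and functional electrical stimulation, each as a 30-minute block in the morning and again in the afternoon, on every weekday.

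**The concern.** An exclusion rule decides whose data are analysed, so it should give one answer for every participant. Here the percentage and the count are joined as equivalents, yet they disagree for a participant who attends 10 of 15 treatments. Nothing in the article says which form governs.

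The trial is small (15 per arm), and only the outcome assessor is blinded. If a participant falls on the disputed count, someone must choose between the two forms, possibly knowing the allocation and after outcomes have been recorded. A fixed rule removes that choice.

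The rule also does not say what is being counted. In the three active arms a reader will naturally take the 15 once-daily sessions. In the control arm the only treatment to count is rehabilitation, which is given twice a day but also totalled as 15.

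**Working it through.** **Inputs.** Threshold 70 %, count below 10, denominator 15 (Data analysis). Added therapies once daily, 5 days a week, 3 weeks (Abstract, Intervention). Rehabilitation twice daily on the same days (Study design, Intervention). 15 participants per arm (Study design).

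**Denominator.** Once daily × 5 days × 3 weeks = 15. The stated total for scalp acupuncture, rTMS and SAEM-CS is reproduced.

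**Threshold.** 0.70 × 15 = 10.5. Attendance is a whole number, so below 70 % means 10 or fewer. Below 10 means 9 or fewer.

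| Treatments received | Share of 15 | Rule: below 70 % | Rule: below 10 |
|---|---|---|---|
| 9 | 9/15 = 60.0 % | eliminated | eliminated |
| 10 | 10/15 = 66.7 % | eliminated | kept |
| 11 | 11/15 = 73.3 % | kept | kept |

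The stated equivalence is not reproduced. Removing those below a percentage gives the same result as removing those below 10 only if that percentage is above 60.0 % and no higher than 66.7 %. A threshold of 70 % lies between 66.7 % and 73.3 % and corresponds to removing those below 11. The two forms disagree at 10 and nowhere else.

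**Weight of one participant.** 1/15 = 6.7 % of an arm.

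**Rehabilitation total.** 2 × 5 × 3 = 30 sessions; 5 × 3 = 15 days. Study design writes twice a day and five times a week side by side. If a time were a single session, twice a day on five weekdays would be 2 × 5 = 10 times a week, so in that sentence a time is most naturally a treatment day, and 15 follows. The Abstract, however, calls the daily pair two sessions, and the Intervention text gives the total of 15 directly after describing sessions. The article does not state which unit it means.

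**Rehabilitation content.** The Intervention text makes electrical stimulation conditional on need, whereas Table 2 schedules it twice every weekday. Table 2 lists physical therapy, which the Intervention text does not name.

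**The case against.** The best defence of the rule is that the parenthesis supplies a usable whole number. A team that applied the count alone would treat everyone consistently, with 70 % as a loose rounding of two thirds. Participants are also in hospital for the three weeks, and the coordinator monitors adherence and manages the schedule, so few should attend exactly 10 times. Both points limit the size of the problem. Neither removes it, because the percentage is stated first, the count is presented as its meaning, and the text gives neither form priority.

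Three stronger readings are tempting, and the article does not support them.

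- A reader might infer that a rehabilitation total of 15 instead of 30 also causes participants to be classified two ways, or that the control arm cannot be judged by the same rule. But 15 can be read as treatment days, a denominator that all four arms share. The two-way classification comes from the mismatch between 70 % and 10 alone. What stands is that the unit should be written down.
- A reader might infer that Table 2 gives three times the daily therapy time of the text. No section states a daily total. If 30 minutes twice daily applies to each therapy, it matches the blocks in Table 2. What stands is the difference over electrical stimulation and physical therapy.
- A reader might want the rule confined to a per-protocol set. That is a question about the choice of analysis population, separate from whether the threshold is stated correctly.

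**Conclusion.** The exclusion threshold is stated wrongly: less than 70 % of 15 is not the same as fewer than 10 of 15. The error is certain arithmetic on the article's own figures and assumes only that attendance is counted in whole units out of the stated 15. It affects participants with exactly 10, each of whom is 6.7 % of an arm of 15. The article gives no attendance distribution, so the number of such participants cannot be estimated; it is probably small. The correction is still worth making, because the rule governs who is analysed in a trial where participants and practitioners know the treatment.

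The rehabilitation descriptions are a secondary matter of wording. The total of 15 has a consistent reading as days, but this is not stated. The text and Table 2 differ on whether electrical stimulation is conditional and on whether physical therapy is named.

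**What to change.** In Data analysis, replace the double statement with one whole-number cut-off that agrees with its percentage. Either eliminate participants with fewer than 11 of 15 and keep 70 %, or keep fewer than 10 of 15 and describe it as less than two thirds. Fix the choice before any outcome data are seen. State that the 15 are treatment days attended, so that the same rule applies to the control arm, which receives rehabilitation only.

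Reconcile the Abstract, Study design, the Intervention text and Table 2 on three points: whether 15 times of twice-daily rehabilitation means 15 days or 30 sessions, whether electrical stimulation is given as needed or scheduled daily, and where physical therapy belongs. Which version is correct is for the investigators to say.

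The cost is wording only; neither the sample size nor the choice of statistical model changes.
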